### Participants

Participant recruitment will run between September 2017 and continue until September 2020 in the early recognition center for psychosis of the Department of Child and Adolescent Psychiatry and Psychotherapy, Psychiatric University Hospital of the University of Zurich (CAPS). The ETRo trial is a naturalistic treatment study. All participants will be help-seeking adolescents (aged 14–18) with at-risk symptoms assessed at the early recognition center. The purpose of the study, the study process, risks, benefits, and alternatives will be explained to all participants and their caregivers according to ethical principles. All participants will be asked to give a written informed consent in accordance with the national law. For inclusion, participants must meet at least one of the following at-risk criteria: 1) at least two self-experienced and self-reported cognitive basic symptoms as assessed by the Schizophrenia Proneness Interview Child and Youth Version (SPI-CY) (71) and/or 2) at least one attenuated psychotic symptom for psychosis assessed by the Structured Interview for Prodromal Syndromes (SIPS) (72).

Exclusion criteria for study participation include a diagnosis of a psychotic disorder, current substance or alcohol dependence, aged below 14, insufficient German or English language ability, or low intellectual abilities with IQ < 75.

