#### Standard Care

The control condition is composed of a control group from a former early recognition study in Zurich (ZInEP) [e.g., Ref. (73)]. The control group consists of 62 adolescents meeting CHR criteria (25 female, age range 13–18 years, mean age 15.06) who historically signed a declaration of consent regarding the use of their data. The sample was accrued from April 2010 to July 2012. The individuals of this subsample of the ZInEP had been treated with non-standardized psychological intervention (TAU) also at the CAPS. Within the ZInEP study, the comparable primary and secondary outcomes (at-risk symptoms, comorbid symptoms, global functioning, self-efficacy, and quality of life) have been evaluated at the same time points (at baseline and 6, 12, 24, and 36 months later). Since we expect a high interindividual variability of symptom fluctuation, reduction, or progression during the phase of intervention, we plan to reduce further putative impact of sex and age and to match individuals from the intervention group to ZInEP individuals accordingly. Consequently, 30 individuals from the ZInEP sample will be included in the statistical analysis.

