### Clinical Analyses

Differences in the primary and secondary outcomes between the two study groups at all time points will be examined with repeated measures analysis of variance and standardized effect sizes (Cohen’s *d*) will be reported. Their respective confidence intervals will be calculated for comparison. Response and remission rates will be compared across groups with contingency tables and differences tested with χ^2^. All unidirectional hypotheses will be tested one sided; bidirectional hypotheses will be tested two sided. Alpha is set to *p* < 0.05. All analyses will be conducted within SPSS.

A linear mixed model approach will be used to assess differences in the primary and secondary outcomes between the two study groups. Logistic regression will be used to assess response and remission rates across the groups. Medication, education, and intelligence will be taken into account as confounding factors by including them in mixed model and logistic regression model, respectively. All unidirectional hypotheses will be tested one sided; bidirectional hypotheses will be tested two sided. Significance level α is set to 0.05.

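### Age and sex are the matching variables but are not among the named model covariates, so residual imbalance goes uncorrected and precision may be lost

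*Protocol article*

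**What the plan says.** Under Standard Care, the protocol article expects high variability between individuals, wants to limit the possible influence of sex and age, and so plans to "match individuals from the intervention group to ZInEP individuals accordingly". It continues: "Consequently, 30 individuals from the ZInEP sample will be included in the statistical analysis". The pool is 62 adolescents, described as "25 female, age range 13–18 years, mean age 15.06". The Participants section gives 14–18 as the age range for the intervention group. The Discussion repeats that the pool is large enough for age and sex matching. No ratio, age tolerance or matching algorithm is given, although 30 controls for 30 treated participants implies 1:1.

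Under Clinical Analyses, the model for primary and secondary outcomes is given as follows: "A linear mixed model approach will be used to assess differences in the primary and secondary outcomes between the two study groups". Logistic regression is named for response and remission. On adjustment, the section says: "Medication, education, and intelligence will be taken into account as confounding factors by including them in mixed model and logistic regression model, respectively". The same section also lists a repeated measures ANOVA and a chi-square test, with no mention of pairing. The Discussion names medication, hospitalization and treatment frequency as confounders that may be controlled for. Age and sex appear in neither list.

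**The concern.** The design treats age and sex as influential enough to decide which controls are used, yet the stated covariate list omits both. Two things could follow.

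- **Residual confounding.** Matching from a finite pool is rarely exact. Any age or sex difference that remains passes straight into the group effect. In a non-randomised comparison with historical controls and one-sided tests of directional hypotheses, a bias in the favourable direction raises the false-positive rate.
- **Lost precision.** Balancing the groups on variables that predict outcome reduces the true variance of the group difference. A model that includes neither those variables nor the pairs does not see that reduction and reports a standard error that is too large. With 30 per group there is little precision to give away.

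**Working it through.** The plan states no figure for residual imbalance or for the gain from matching, so there is none to reproduce. Its sample sizes (Table 2: SIPS 17, SPI-CY 16, SWE 27 per group) cannot be rebuilt either, because SD and power are not given. Working backwards at 80% or 90% power, one- or two-sided, they imply SDs of 13.1–17.2, 7.6–10.0 and 4.5–5.8.

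**1. Scope for inexact matching (figures from Standard Care and Participants).** The pool has 25 females and 62 − 25 = 37 males. Exact 1:1 sex matching without replacement fails if more than 25 of the 30 treated participants are female. Controls aged 13 have no same-age counterpart. The pool's mean age is 15.06, so an older treated group would draw on its thinner upper end.

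**2. Standard error under exact matching.** Take outcome variance σ², n = 30 per group and within-pair correlation ρ. The unpaired analysis uses variance 2σ²/n, while the true variance is 2σ²(1 − ρ)/n. With exact matching, ρ equals the share of variance that age and sex explain (R²). The standard error is therefore too large by the factor 1/√(1 − R²), and the actual one-sided level at nominal 0.05 is 1 − Φ(1.645 × factor).

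| R² (assumed) | Factor | Actual one-sided level |
|---|---|---|
| 0 | 1.00 | 0.050 |
| 0.05 | 1.03 | 0.046 |
| 0.10 | 1.05 | 0.042 |
| 0.20 | 1.12 | 0.033 |
| 0.30 | 1.20 | 0.025 |

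In SD units the unadjusted standard error is √(2/30) = 0.258. The true values at R² of 0.10, 0.20 and 0.30 are 0.258 × √0.90 = 0.245, 0.258 × √0.80 = 0.231 and 0.258 × √0.70 = 0.216.

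**3. Residual imbalance.** This was simulated with 5,000 runs per setting: 30 treated participants matched 1:1 to the 62 controls, exactly on sex and to the nearest age, with one continuous endpoint and no true effect. Assumptions not found in the documents: control age SD 1.4; treated age SD 1.3; treated mean age 15.1, 15.8 or 16.3; half of the treated female; the R² values. The age effect was set so that bias runs in the direction tested; in practice it could run either way.

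| Treated mean age | Age gap left (years) | R² | Bias, unadjusted (SD) | One-sided type I error, unadjusted | With age and sex |
|---|---|---|---|---|---|
| 15.1 | 0.03 | 0.10 | 0.006 | 0.044 | 0.049 |
| 15.1 | 0.04 | 0.30 | 0.011 | 0.040 | 0.059 |
| 15.8 | 0.17 | 0.10 | 0.026 | 0.057 | 0.051 |
| 15.8 | 0.17 | 0.30 | 0.049 | 0.050 | 0.050 |
| 16.3 | 0.41 | 0.10 | 0.073 | 0.076 | 0.047 |
| 16.3 | 0.40 | 0.30 | 0.118 | 0.095 | 0.048 |

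At R² = 0 the unadjusted level was 0.050–0.054. With age and sex in the model, bias stayed within 0.005 SD in every setting. A paired analysis without covariates did not repair the problem: at R² = 0.30 its type I error was 0.065, 0.077 and 0.136 for the three mean ages.

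**4. Power.** This depends heavily on the assumed effect. In a separate simulation of exactly matched pairs at d = 0.6 (two-sided 0.05), power without and with age and sex was 64% and 68% at R² = 0.10, 63% and 72% at 0.20, and 66% and 78% at 0.30. At d = 0.87, the low end of what Table 2 implies for SIPS, the corresponding figures are 92.8% and 94.0%, 93.6% and 95.7%, and 94.3% and 97.8%.

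**The case against.** The article condenses a fuller plan, and pair handling and the complete covariate list often sit in the analysis plan. One can read the two sections as a division of labour, with age and sex dealt with by design and other confounders by model. This stands to a degree: a pair term is unstated, not excluded, because the random-effect structure is not given. It does not dispose of the point, because the article does commit to a covariate list for both models, and pairing alone would not correct residual imbalance.

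Three stronger conclusions are tempting, and the documents do not support them.

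- **That the standard errors are simply wrong, or the tests invalid.** The effect is conditional. It vanishes if age and sex do not predict outcome, and the article itself calls their impact putative. Where they do predict, the error in the standard error makes the test conservative.
- **That the loss of power is large.** The R² values and d = 0.6 are assumptions. The primary outcomes include changes, in which stable age and sex differences may largely cancel. Education may also stand in for part of age: with an assumed correlation of 0.8, at 20% explained variance, it brings the standard error from 0.257 to 0.250, against 0.230 with age and sex. At effects of the size that Table 2 implies for SIPS, the loss is about 1 to 3.5 percentage points, though it would be larger at the lower bound for SWE (d about 0.69).
- **That the logistic odds ratio is biased toward 1.** The shift between an unadjusted and a covariate-adjusted odds ratio is largely a change of estimand, not in itself an error.

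**Conclusion.** The point holds as a gap between design and stated analysis. Age and sex determine which controls are chosen, but the named models neither adjust for them nor name the pairs. If matching is close, bias is negligible (about 0.01 SD at 30% explained variance) and the cost is precision only. If the treated group is clearly older than the pool, bias reaches about 0.12 SD at 30% explained variance, with one-sided type I error near 0.095. That is the worst case examined, and it rests on an assumed treated mean age of 16.3 and assumed age spreads. The 5%, 12% and 20% excess in standard error rests on exact matching and on assumed explained variance of 10%, 20% and 30%. The documents give none of these inputs. The change is worth making because it is specific and nearly free, not because the planned analysis is shown to be invalid.

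**What to change.** In Clinical Analyses, add baseline age and sex as fixed covariates in the linear mixed model, alongside medication, education and intelligence. Add them to the logistic regression too where the number of response or remission events allows. The same sentence could state the age tolerance used in matching and whether pairs are modelled.

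The cost is one sentence and two degrees of freedom; both variables are already needed for the matching. The downside lies in the logistic model, which already carries group and three covariates for 60 participants: two more terms could strain it if events are few.

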### Primary Outcome

Primary outcome measures are transition to psychotic disorders, changes in at-risk as well as comorbid symptomatology, global functioning, life quality, and self-efficacy. All these measures will be compared with those of the control group.

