## Abstract

**Introduction:** The prevention of schizophrenia and other psychotic disorders has led researchers to focus on early identification of individuals at clinical high risk (CHR) for psychosis and to treat the at-risk symptoms in the pre-psychotic period. Although at-risk symptoms such as attenuated hallucinations or delusions are common in adolescents and associated with a marked reduction in global functioning, the evidence base of effective interventions for adolescents at CHR state and even ﬁrst-episode psychosis is limited. Thus, the present protocol describes a study design that combines therapy modules for CHR adolescents with a smartphone application supporting the young individuals between the therapy sessions. The treatment approach “Robin” is based on existing therapy strategies for adolescents with first episode of psychosis and the available recommendations for adults with at-risk symptoms.

**Methods:** The evaluation aims firstly to compare the efficacy of Robin in 30 CHR adolescents aged 14–18 to an active control group (treatment as usual) from a previous study. Primary outcome measures will be at-risk symptomatology, comorbid diagnosis, functioning, self-efficacy, and quality of life. For the prospective intervention condition (16 weekly individual sessions + a minimum 4 family sessions), help-seeking adolescents with CHR for psychosis, aged 14–18, will be recruited over 3 years. At-risk and comorbid symptoms, functioning, self-efficacy, and quality of life are monitored at six time points (baseline, during the treatment period; immediately after intervention; and 6, 12, and 24 months later) and compared with the respective measures of the active control group.

**Discussion:** To the best of our knowledge, this is the first controlled trial to test the efficacy of a specific early psychosis treatment in combination with a smartphone application for adolescents at CHR for developing psychosis. The results of the study are expected to add information that may substantially decrease the burden of CHR adolescents and increase their resilience. It may offer age-adapted and targeted strategies to guide clinicians in the treatment of these vulnerable individuals. Furthermore, research in the field of early intervention will be enriched by our findings.

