### Assessment

At baseline, demographic variables, past psychiatric illness, and treatment information are obtained from the participants and their caregivers. Before participating in the study, all patients will undergo a clinical assessment and diagnostic process according to *International Classification of Diseases*, Tenth Revision, criteria. Adolescents will be asked to complete a questionnaire about their personality traits PSSI (74) and to perform the Wechsler Intelligence Scale for Children (75) or Wechsler Adult Intelligence Scale for individuals aged > 16 years 11 months (76) to evaluate their cognitive profile.

In accordance with EPA guidance on the early detection of CHR states of psychoses, the CHR status is assessed with the Schizophrenia Proneness Interview Child and Youth Version (71) and the Structured Interview for Prodromal Syndromes (72). All investigators are either psychologists or psychiatrists. They are trained to a “gold standard,” and reliability will be measured for the duration of the trial. Comorbid mental disorders will be screened for with the Mini-International Neuropsychiatric Interview for Children and Adolescents based on *Diagnostic and Statistical Manual of Mental Disorders*, Fourth Edition (77). The severity of depression will be measured using theHamilton Depression Scale (78).

Information about functioning will be measured with the Global Assessment of Functioning Scale (GAF) (79), Social and Occupational Functioning Assessment (SOFA) Scale (80), and Global Functioning: Social Scale (GF: Social) (81). Data about quality of life, personality traits, and self-efficacy will be collected using the Manchester Short Assessment of Quality of Life (MANSA) (82) and the General Self-Efficacy Scale (SWE) (83).

Treatment satisfaction will be evaluated with the treatment evaluation questionnaire for adolescent patients FFB-J (84). A feedback form created specifically for the app will gather information regarding acceptance and contentment with the smartphone application Robin Z (**Table 1**).

**Table 1 T1:** Description of assessments from baseline to endpoint of study.

	Baseline	Intervention (16 session)		Follow-up		
**Time point (months)**	**0**	**2**	**4**	**6**	**12**	**24**
Socio‐demographic characteristics	x	x	x	X	x	x
Clinical diagnosis according to**** *ICD-10* Re-evaluation of all diagnoses	x	x	x	X	x	x
Medication	x	x	x	X	x	x
Intellectual ability: WISC/WAIS	x					
Personality traits: PSSI	x					x

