## Discussion

Despite evidence suggesting that young individuals with at-risk symptoms may profit best from specialized treatment approaches (85), little is known about age-appropriate treatment strategies in this vulnerable age group (15). The treatment program Robin has been developed to fill this gap.

Our treatment approach Robin is an integrated approach based not only on CBT but also on systemic therapy. The treatment is both solution and resource focused. Furthermore, Robin is an individualized treatment approach in line with the individual needs of the particular patients, which should lead to a high acceptance. Furthermore, age-appropriated treatment material, including a smartphone app and the involvement of the family, may result in higher engagement in therapy (32, 41, 49). The smartphone application Robin Z has been developed to enrich the treatment and to increase treatment satisfaction through providing support between sessions. Previous studies have already demonstrated that mobile-based interventions are feasible and accepted by psychotic patients (49, 58, 59, 66); thus, we expect the same for CHR individuals.

In accordance with EPA guidance in early intervention in CHR states of psychoses (15), a primary aim of this treatment approach is to improve the daily functioning. Thus, the study group decided to primarily focus on quality of life, self-efficacy, and functioning. These areas have been shown to be most impacted in adolescents and often prompt them to seek help (18, 30, 44, 86, 87). In contrast, at-risk symptoms are not necessarily the cause of the highest psychological strain and burden for the patient. Furthermore, we expect a remission or at least a significant decline of the at-risk symptoms in most patients after the treatment period. Prior evidence has demonstrated that at-risk symptoms, especially in adolescents, show high levels of fluctuation (70, 88). How much this fluctuation symptoms or remission rates are associated with a specific intervention is currently unknown. Our first analysis of symptomatology in the control group also showed a high reduction of at-risk symptoms during follow-up compared with the baseline.

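### The primary outcome is not fixed: six unranked domains, lists that disagree and no multiplicity control at alpha 0.05, so the familywise false-positive rate is substantially inflated

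*Protocol article*

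**What the plan says.** **Outcome lists.** The Primary Outcome section reads "Primary outcome measures are transition to psychotic disorders, changes in at-risk as well as comorbid symptomatology, global functioning, life quality, and self-efficacy", with no ranking. The Abstract reads "Primary outcome measures will be at-risk symptomatology, comorbid diagnosis, functioning, self-efficacy, and quality of life". It leaves out transition and has comorbid diagnosis where the Primary Outcome section has comorbid symptomatology. The Discussion adds "Thus, the study group decided to primarily focus on quality of life, self-efficacy, and functioning" and then sets at-risk symptoms apart.

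**Instruments.** The Assessment section and Table 1 give nine scales for these domains:
- at-risk state: SPI-CY and SIPS
- comorbidity: MINI-KID and HAMD
- functioning: GAF, SOFAS and GF: Social
- quality of life: MANSA
- self-efficacy: SWE

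Transition is a further event outcome.

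**Hypotheses.** At the end of the Introduction, Hypothesis 2 (quality of life and self-efficacy) and Hypothesis 3 (clinical and functional remission rates) are directional comparisons with TAU at 6, 12 and 24 months.

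**Testing.** Clinical Analyses says "All unidirectional hypotheses will be tested one sided; bidirectional hypotheses will be tested two sided", with alpha 0.05. It describes repeated measures ANOVA and χ² tests, then a linear mixed model and logistic regression for the same outcomes.

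**Sizing.** Sample Size treats each instrument separately at 6 months: SIPS 17, SPI-CY 16 and SWE 27 per group, with 30 chosen.

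**The concern.** A confirmatory claim needs a result named in advance that decides it. Here the reader cannot tell which domain, instrument, visit or model that is, or how many domains must succeed. The article fixes several primaries and one unadjusted alpha itself, so this is more than a detail left to an analysis plan.

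The design is also exposed. Controls are historical and not randomised, and the Discussion reports that control-group symptom data have already been examined. With one arm partly known and no ranked primary, emphasis could follow the data. One-sided testing at 0.05 is equivalent to a two-sided 0.10 standard for the hypotheses it covers, and as a formal test it cannot declare a worse outcome under Robin.

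**Working it through.** **1. The plan's own figure.** The article states no familywise error rate. Its only related figures are the sample sizes in Table 2. These cannot be reproduced, because SD, power and sidedness are not given. Solving SD = δ / [(z_α + z_power) × √(2/n)] at alpha 0.05, one- or two-sided, with power assumed at 80% or 90%, gives:

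| Instrument | δ | n per group | Implied SD |
|---|---|---|---|
| SIPS | 15 | 17 | 13.5–17.6 |
| SPI-CY | 9 | 16 | 7.9–10.2 |
| SWE | 4 | 27 | 4.5–5.9 |

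Table 2 is neither confirmed nor refuted. Each row is a single test with no allowance for multiplicity.

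**2. Independent tests.** P(at least one false positive) = 1 − 0.95^k:
- k = 3 (Discussion focus): 14.3%
- k = 5 (Abstract): 22.6%
- k = 6 (Primary Outcome): 26.5%
- k = 9 (instruments): 37.0%

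**3. Correlated tests.** These come from 200,000 multivariate normal draws of one-sided tests at 0.05. The correlations are assumed.

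| Tests | r = 0.3 | r = 0.5 | r = 0.7 |
|---|---|---|---|
| 6 domains | 22.0% | 18.7% | 14.8% |
| 9 instruments | 28.8% | 23.4% | 17.8% |

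**4. Sidedness.** If every test were two-sided, a false result favouring Robin would have probability 0.025 per test. For six independent tests, 1 − 0.975^6 = 14.1%, against 2.5% for a single test. If only quality of life and self-efficacy were one-sided, the figure is 1 − 0.95² × 0.975⁴ = 1 − 0.9025 × 0.9037 = 18.4%.

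**5. Worst case.** Separate tests at each of three follow-ups would give 18 or 27 tests: 60.3% or 75.0% if independent, and 27–44% or 32–54% with correlations of 0.3–0.7 between outcomes and 0.5–0.7 between visits.

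**6. Power under adjustment.** Bonferroni over six domains uses 0.05/6 = 0.0083 per test. With the implied SDs and 30 per group, power = Φ(δ / [SD × √(2/30)] − z). For SWE with SD 5.91, one-sided: 4 / (5.91 × 0.2582) = 2.62, and Φ(2.62 − 2.39) ≈ 59%. With SD 4.53, two-sided: 3.42 − 2.64 = 0.78, so about 78%. Unadjusted SWE power on the same assumptions is 84–93%. Adjusted power stays at 82–95% for SIPS and 84–96% for SPI-CY.

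**The case against.** A reader might infer more than the text supports, in four ways.

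- **Every outcome is tested one-sided.** The rule is conditional. Only Hypotheses 2 and 3 are clearly directional comparisons; transition and change in symptom scores have no stated direction, and an ANOVA F test has none. Cohen's d with confidence intervals is also planned, so a worse result would be visible even where the one-sided test could not declare it.
- **There are 18 or 27 separate tests.** Time points are modelled jointly by ANOVA or mixed model. Hypotheses 2 and 3 name three follow-ups, but for their own outcomes and not for all nine scales. Those counts are a worst case.
- **A chance success is likely.** Beyond 50% is reached only with 18–27 independent tests or 27 weakly correlated ones. That is implausible for overlapping scales in the same patients.
- **There are three formal endpoint lists.** Only the Abstract and Primary Outcome are formal lists. The Discussion describes emphasis and is a weaker conflict.

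It can also be said that Sample Size points to a smaller family. It speaks of main instruments at 6 months, and its abbreviation key names four (SIPS, SPI-CY, SWE, GAF). Even so, four independent tests give 1 − 0.95⁴ = 18.5%, and that section sets no hierarchy.

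These points limit the size of the problem and the wording of the claim. They do not supply the missing hierarchy, adjustment or deciding model.

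**Conclusion.** The concern holds in this form. The primary outcome is defined inconsistently and without rank, and a single unadjusted alpha of 0.05 applies to all of it. The familywise false-positive rate is about 15–26% at one test per domain and about 18–37% at one test per instrument, roughly three to seven times nominal. The upper ends assume independence; the lower ends assume correlations up to 0.7, which the article does not give. The correlated figures also assume one-sided tests throughout. Under two-sided testing the error in Robin's favour is smaller, but still well above its intended level. The unresolved choice between two sets of models adds further freedom that is not quantified here. The supportable description is substantially inflated error, not a probable false success.

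**What to change.** **Preferred.** Name one primary outcome, one instrument, one time point and one model. Six months is the natural time point because the trial is sized there. SWE is one candidate consistent with the document: it belongs to Hypothesis 2 and to the Discussion's focus, and it has the largest legible N in Table 2 (the GAF row is not readable, but the stated range of 16 to 27 allows it at most a tie). Quality of life and functioning are also in the Discussion's focus. The choice is the sponsor's and should be made before the outcome data are compared between groups.

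**Alternative.** Keep one named instrument per domain and apply Holm.

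**Either way.** Make the remaining scales and months 12 and 24 secondary with confidence intervals. Test two-sided at 0.05 (or one-sided at 0.025). State which model decides. Align the Abstract, Primary Outcome, Clinical Analyses, Sample Size and Discussion.

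**Cost.** The threshold is stricter and some power is lost per outcome. Under Bonferroni over six domains, SWE power at 30 per group would be roughly 59–78%, if Table 2 was built on 80–90% power; Holm is never less powerful than Bonferroni. Using all 62 ZInEP controls should not be counted on to recover the loss: that rests on unstated power and sidedness, and it would change the matched-30 design in Standard Care. Recruitment began in September 2017, so the change needs a dated, documented amendment.
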